## Adaptations to the original CETA manual

For the current trial, we made the following adaptations to the CETA manual. In the two cognitive restructuring modules, we excluded two skills (providing facts and logical questioning). We also decided to start every first cognitive restructuring two sessions with the friend/family role-play skill. For the exposure module, we defined three different types of exposure (imaginative exposure, in vivo exposure, and interoceptive exposure) and will tailor these to the patients. Furthermore, we opened the substance abuse module for patients reporting gambling problems. In the problem-solving module, we specifically probe for problems related to postmigration stressors like discrimination.

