#### Outcomes {12}

Patient outcome measures consist of self-report questionnaires, which are assessed at baseline (week 0), at week 1, at mid-treatment (week 5), at post-treatment (last session/week 12), and, for the active condition, at 3-month (week 24) and 6-month follow-up (week 36). The primary endpoint is at post-treatment (12 weeks after randomization for the waitlist group).

All questionnaires will be presented via the platform that also hosts the CETA-I intervention. See Table 2 and the section “Data collection and management” for details of measurements at all time points.

**Table 2 Tab2:** Schedule of enrolment, interventions, and assessments

		**Enrolment**	**Allocation**	**Post-allocation**				
**Assessment/activity**		**Baseline**		**Week 1**	**Week 5**	**Post**	**3-month follow-up**	**6-month follow-up**
**Enrolment**	Eligibility screen	x						
	Informed consent	x						
	Allocation		x					
**Intervention**	CETA-I							
	Waitlist							
**Questionnaires for patients**	Sociodemographics	X						
	Healthcare utilization (FIMA & FIMPsy)	X				X		X
	Mental distress, anxiety, depression (HSCL-25)	X			X	X	X	X
	Posttraumatic stress symptoms (PCL-5)	X			X	X	X	X
	Alcohol use (AUDIT)	X			X	X	X	X
	Drug use (DUDIT)	X			X	X	X	X
	Behavioral addictions (own instrument)	X			X	X	X	X
	Health-related quality of life (EQ-5D-5L)	X				X	X	X
	Social support (OSSS-3)	X				X	X	X
	Self-efficacy (GSE)	X				X	X	X
	CBT skills (CBT-SQ)	X				X		
	Outcome expectations (three items)			X				
	Postmigration living difficulties (PMLD-short version)			X				
	Working alliance (WAI-I)				X	X		
	Treatment satisfaction (CSQ-I)					X		
	Negative Effects Questionnaire (NEQ)					X		

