#### Concealment mechanism {16b}

After participants complete the baseline assessment and diagnostic interview, the platform randomizes them to one of the two groups.

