### Assignment of interventions: blinding

#### Who will be blinded? {17a}

Due to the nature of psychotherapeutic treatment trials, neither participants therapists nor study personnel can be blind to treatment allocation.

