### Predictors and moderators of treatment outcome

To assess potential predictors and moderators of treatment outcomes, we will use the baseline scores of the secondary outcomes measuring PTSD, depression, anxiety, and substance abuse symptoms as described above. We will also assess sociodemographic and asylum-related variables (e.g., length of stay, asylum status), post-migration stressors (using 11 items of the Post-Migration Living Difficulties Scale (PMLD)-Short Version [60, 61]), self-efficacy (using the 12-item General Self-efficacy Scale (GSE) [62]), and social support (using the 3-item Oslo Social Support Scale (OSSS-3) [63]).

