#### Methods for additional analyses (e.g., subgroup analyses) {20b}

To evaluate differential treatment effects, the interaction effects of moderators with treatment on the outcome will be tested. Exploratory mediation analyses will be conducted.

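### Post-migration living difficulties are listed as a predictor/moderator but scheduled only at week 1, after open randomisation, unlike the other scheduled measures on that list

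*Protocol article*

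**What the plan says.** The section on predictors and moderators opens with the symptom scales, which are to be used at their baseline values: "To assess potential predictors and moderators of treatment outcomes, we will use the baseline scores of the secondary outcomes". It then adds sociodemographic and asylum-related variables, "post-migration stressors (using 11 items of the Post-Migration Living Difficulties Scale (PMLD)-Short Version", self-efficacy and social support. Under additional analyses {20b}, "the interaction effects of moderators with treatment on the outcome will be tested".

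The Outcomes section {12} describes questionnaires "which are assessed at baseline (week 0), at week 1, at mid-treatment (week 5" and later, so baseline and week 1 are separate occasions. In Table 2 the row "Postmigration living difficulties (PMLD-short version" is marked once, at week 1, in the post-allocation block.

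On the order of events, the concealment section {16b} states: "After participants complete the baseline assessment and diagnostic interview, the platform randomizes them to one of the two groups". On blinding, section {17a} states that "neither participants therapists nor study personnel can be blind to treatment allocation".

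**The concern.** A treatment moderator should be a characteristic that the participant brings to randomisation. Only then does a treatment-by-moderator interaction answer whether the effect differs between people who were different at the start. A variable recorded after allocation may itself have been changed by the arm.

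The protocol leaves two routes open. The PMLD is a self-report completed by people who know whether they will be treated now or wait 3 months. The intervention can also touch the same construct: in the problem-solving module, "we specifically probe for problems related to postmigration stressors like discrimination". In addition, anyone who stops responding before week 1 has no value.

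At stake is the interpretation of the PMLD as a predictor or moderator. No analysis plan written later can recover a pre-randomisation value that was never collected.

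**Working it through.** **1. Timing, from the documents.** Reading the Table 2 rows against the column headers:

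- Sociodemographics: baseline only.
- HSCL-25, PCL-5, AUDIT, DUDIT: baseline, week 5, post-treatment and both follow-ups.
- Self-efficacy (GSE) and social support (OSSS-3): baseline, post-treatment and both follow-ups.
- PMLD: week 1 only.
- Outcome expectations: week 1 only. These are named as mediators, for which a post-allocation time is appropriate.

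The PMLD is the one scheduled measure on the predictor/moderator list without a baseline mark. Randomisation follows the baseline assessment, so the only PMLD value is post-randomisation. No reason for the timing is given.

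**2. Plan's own figure.** The plan attaches no number to this point. The sample-size section supplies only the allocated numbers used below, 75 (CETA-I) and 56 (waitlist).

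**3. Constant shift.** Let A be the arm, M the baseline PMLD in SD units and M1 = M + sA the week-1 value. Suppose Y = τA + βM + γAM + e. Substituting M = M1 − sA gives

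Y = (τ − βs − γs)A + βM1 + γA·M1 + e.

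The interaction γ is unchanged; only the treatment coefficient moves. With assumed τ = −0.60, β = 0.4, γ = 0 and s = −0.2, the coefficient becomes −0.60 + 0.4 × 0.2 = −0.52.

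**4. Change that also tracks response.** Now let M1 = M + A(s + hU), where U is an individual response component with assumed loading 0.5 on Y in the treated arm. The slope of Y on M1 is (0.4 + 0.5h)/(1 + h²) in the treated arm and 0.4 in the waitlist arm. The spurious interaction is the difference, and the treatment coefficient is −0.60 − slope × s.

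- h = 0.3, s = −0.2: slope 0.55/1.09 = 0.505; interaction 0.105; coefficient −0.50.
- h = 0.5, s = −0.2: slope 0.65/1.25 = 0.52; interaction 0.12; coefficient −0.50.
- h = 0.7, s = −0.3: slope 0.75/1.49 = 0.503; interaction 0.103; coefficient −0.45.

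**5. Simulation.** 75 against 56 participants, all observed; least squares with interaction and HC3 errors; 1,500 runs per setting; no true moderation by baseline PMLD.

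| s | h | Type I error, week-1 PMLD | Type I error, baseline PMLD | Interaction, week-1 | Treatment coefficient, week-1 |
|---|---|---|---|---|---|
| 0 | 0 | 0.053 | 0.053 | −0.002 | −0.602 |
| −0.2 | 0 | 0.049 | 0.049 | −0.003 | −0.524 |
| −0.2 | 0.3 | 0.099 | 0.053 | 0.103 | −0.498 |
| −0.2 | 0.5 | 0.118 | 0.055 | 0.124 | −0.495 |
| −0.3 | 0.7 | 0.090 | 0.047 | 0.100 | −0.446 |

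The simulation agrees with the algebra. All values of s, h, β and the response loading are assumptions; the documents give none.

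**6. Could the trial detect a shift?** With everyone responding, the standard error of the arm difference in week-1 PMLD is √(1/75 + 1/56) = 0.177 SD. Power of 80% needs about 2.80 × 0.177 = 0.49 SD. Shifts of 0.2–0.3 SD would usually go unnoticed, and there is no baseline value to compare with.

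**The case against.** The strongest reply is that this is peripheral. The primary and secondary comparisons are baseline-adjusted regressions that do not name the PMLD. The Objectives put the moderator focus on baseline symptoms, which are measured before randomisation. The PMLD is one entry in a list of potential predictors and moderators, and section {20b} names no variable, so a PMLD-by-treatment test is a reasonable inference rather than an explicit commitment. Participants are asked to do one session a week, so exposure by week 1 is small, and the problem-solving module goes only to those who qualify for it. All of this stands, and it limits the weight of the point. It does not remove the mismatch between the listed use and the schedule.

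A reader might also infer more than the documents support:

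- **That the trial's effect is distorted by 5–25%.** Assumed shifts of 0.1–0.3 SD and slopes of 0.3–0.5 give 0.1 × 0.3 = 0.03 to 0.3 × 0.5 = 0.15 SD, which is 5–25% of d = 0.6. Both inputs are assumed, and the result concerns the treatment coefficient in the moderator model. It is neither the interaction test nor the primary effect.
- **That the moderator is lost unequally because attrition is 40% and 20%.** Those are overall planning rates. No week-1 loss is stated, and multiple imputation is planned for the ITT analyses.
- **That any PMLD interaction is meaningless.** If allocation does not alter the PMLD, or shifts it by a constant, the interaction coefficient is intact.
- **That post-migration context is otherwise unmeasured.** The PMLD is the only named scale for these stressors, but length of stay and asylum status are also listed.

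**Conclusion.** The point holds as a minor but real design flaw. A listed predictor/moderator is measured only after open randomisation, while the other scheduled measures on the list are taken at baseline. Allocation or early treatment could alter it; the documents do not show that either will, and a change within one week may be small.

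Under the assumed values, a uniform 0.2 SD shift moves the conditional treatment coefficient from −0.60 to −0.52 and leaves the interaction test at its nominal level. A type I error of 0.09–0.12 requires the further assumption that early PMLD change tracks treatment response. Participants who stop before week 1 lack the measure, in unknown number. The primary analysis, the baseline-symptom moderators and the sample size are not affected.

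**What to change.** Move the 11-item PMLD in Table 2 from week 1 to the pre-randomisation baseline battery, and use that value for predictor and moderator analyses. The cost is a slightly longer baseline assessment, which already carries 11 measures; the scale is removed from week 1, so the total number of items is unchanged.

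Recruitment was due to start in November 2023, so some participants may already have been randomised without a baseline value. For them, label the week-1 PMLD as a post-randomisation variable, report it by arm, and do not interpret its interaction with treatment as baseline effect modification. Using it in the imputation model remains acceptable. If the scale moves partway through recruitment, report how many of the planned 131 participants have a pre-randomisation value.

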	**Weekly assessments**							
	Mental distress (PHQ-4)							
	PTSD (PCL-5-short version)							
	Drug and alcohol use							
	Suicidal ideation, domestic violence, aggressive behaviors (single items)							

#### Participant timeline {13}

Figure 1 depicts the participants’ anticipated flow.

**Fig. 1 Fig1:**
[figure not shown]
Anticipated participant flow

#### Sample size {14}

A pragmatic viewpoint was taken in planning the sample size. We assumed that the difference between active treatment and waitlist conditions is between *d* = 0.6–0.8 [30]. Both effects flag clinical meaningful between-group differences. Using an alpha of 5% (two-sided test), randomizing *N* = 44 individuals to each study arm would result in a power of 80% (> 95%) for comparing the WL against the CETA-I condition with *d* = 0.6 (*d* = 0.8). To avoid that the sample becomes too small, we used *n* = 44 for further planning. Two RCTs on CETA [29, 30] reported moderate attrition rates in the treatment (1 to 18%) and waitlist group (4 to 23%). In the RCT on online treatments of Arabic-speaking patients [24], patients showed an attrition rate of 40%. To compensate for dropout, we conservatively assume an attrition rate of 20% in the waitlist group and 40% in the CETA-I condition. Thus, we allocate *N* = 131 individuals (CETA-I: 75; waitlist: 56).

#### Recruitment {15}

Participants will be mainly recruited through the Internet using Google and Facebook ads and through postings in relevant social media groups and mental health forums.

### Assignment of interventions: allocation

#### Sequence generation {16a}

A randomization mechanism is hard coded into the online platform that hosts the intervention.

#### Concealment mechanism {16b}

After participants complete the baseline assessment and diagnostic interview, the platform randomizes them to one of the two groups.

#### Implementation {16c}

We will apply a simple randomization procedure, with no blocks or stratification. The randomization list will be prepared by an independent investigator unrelated to the study using the sealed envelope web app. The list will be transferred directly to the software development agency which will integrate the list into the randomization tool of the platform. Study investigators, therapists, or others have no access to the randomization list or tool and cannot influence randomization at any point.

### Assignment of interventions: blinding

#### Who will be blinded? {17a}

Due to the nature of psychotherapeutic treatment trials, neither participants therapists nor study personnel can be blind to treatment allocation.

#### Procedure for unblinding if needed {17b}

The design is open label, so unblinding for study coordinators will not occur.

### Data collection and management

#### Plans for assessment and collection of outcomes {18a}

Table 2 gives an overview of the assessment plan. The *primary outcome* is mental distress, assessed by the total score of the HSCL-25, self-report version. The 25 items of the HSCL assess mental health symptoms on a 4-point Likert scale. The questionnaire has been validated in refugee populations and showed good psychometric properties [43, 44].

#### Secondary outcomes

As secondary outcomes, we will assess *depression* with the 15-item HSCL-25 *depression* subscale and *anxiety* with the 10-item HSCL-25 anxiety subscale. The use of the total score and the subscale scores is supported by results on the factorial validity of the HSCL-25 in Arabic-speaking samples. Two studies show a clear distinction between depression and anxiety factors as well as an overall factor capturing mental distress [44, 45]. While one study [44] found two “anxiety” factors (seven items loading on a general anxiety factor and three factors loading on a “phobic anxiety” factor), it seems justified to combine these two factors when investigating anxiety disorders in a transdiagnostic approach.

## PTSD

At pre-assessment, participants will indicate whether they have ever experienced a traumatic event. *Posttraumatic symptoms* will then be assessed with the PCL-5 [36]. The PCL-5 assesses PTSD symptoms according to DSM-5 with 20 items (total score range 0–80). The Arabic and Farsi versions of the PCL-5 showed good psychometric properties [46, 47].

## Addictions

Problematic alcohol and drug use will be assessed by the 10-item AUDIT [48–50] and 11-item DUDIT [51, 52] questionnaires respectively. The Arabic AUDIT and DUDIT showed good reliability and validity [50, 52] as did the Farsi versions [53, 54]. For assessing *pathological gambling* and other addictive behaviors, we developed six items, rated on a 5-point Likert scale, depicting DSM-5 criteria of pathological gambling.

To monitor *treatment progress over time*, we will include a brief measure on mental distress (Patient Health Questionnaire-4 (PHQ-4) [55]); the 4-item short version of the PCL-5 [56]; three questions screening for suicidal ideation, domestic violence, and aggressive behaviors; and four questions depicting the use of and craving for alcohol or drugs as weekly measures.

To assess *health-related quality of life*, we will administer the EQ-5D-5L. On six items, the EQ-5D-5L assesses general health and quality of life in five different domains (e.g., mobility, and daily activities). It is available in Arabic and Farsi and shows excellent psychometric properties across a broad range of populations, conditions, and settings [57].

We will assess *patient satisfaction* with an adapted version of the Client Satisfaction Questionnaire for Internet-based treatments (CSQ-I) [58]. Potential *side effects* of treatment will be assessed using the 20-item version of the Negative Effects Questionnaire [59].

### Predictors and moderators of treatment outcome

To assess potential predictors and moderators of treatment outcomes, we will use the baseline scores of the secondary outcomes measuring PTSD, depression, anxiety, and substance abuse symptoms as described above. We will also assess sociodemographic and asylum-related variables (e.g., length of stay, asylum status), post-migration stressors (using 11 items of the Post-Migration Living Difficulties Scale (PMLD)-Short Version [60, 61]), self-efficacy (using the 12-item General Self-efficacy Scale (GSE) [62]), and social support (using the 3-item Oslo Social Support Scale (OSSS-3) [63]).

#### Mediators of treatment outcome

As potential mediators, we will assess working alliance (using an adapted version for Internet-based treatments (WAI-I) [64]), outcome expectations and perceived barriers [65], and CBT skills (using the Cognitive-Behavioral Therapy Skills Questionnaire (CBT-SQ) [66].

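### Perceived barriers are a named mediator with no labelled row or visit in Table 2, and outcome expectations have no pre-allocation score to adjust for

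*Protocol article*

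**What the plan says.** The section on mediators of treatment outcome names four candidates: working alliance, outcome expectations, perceived barriers and CBT skills. The middle two appear as one phrase with one citation, "outcome expectations and perceived barriers [65".

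Outcomes {12} says that patient measures are "assessed at baseline (week 0), at week 1, at mid-treatment (week 5), at post-treatment (last session/week 12", with later follow-ups for the active arm, and refers to Table 2 for what is measured when. Section {18a} likewise presents Table 2 as the overview of the assessment plan. The row "Outcome expectations (three items" has a single mark, in the week 1 column. No row is labelled perceived barriers, and no other section gives them an item count or a visit.

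Section {16b} places randomization after the baseline assessment and the diagnostic interview. On blinding, {17a} states that "neither participants therapists nor study personnel can be blind to treatment allocation". Mediators are to be examined with regression models ({20a}), and {20b} gives their status: "Exploratory mediation analyses will be conducted".

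**The concern.** There are two separate gaps.

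First, the text commits to assessing a mediator that the schedule does not show. If the schedule is complete, that mediator will not be available for analysis. If another row includes it, the reader cannot tell which items measure it.

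Second, outcome expectations have no value from before allocation. People who are hopeful before they learn their arm may score higher at week 1 and may also do better on the HSCL-25 at post-treatment for reasons unrelated to the week 1 score. Randomization does not protect the association between mediator and outcome, so part of an estimated indirect effect could come from prior expectation. At stake is the interpretation of an exploratory analysis. The primary and secondary comparisons and the sample size are unaffected.

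**Working it through.** The plan attaches no figure to this point, so there is none to reproduce. The check compares text with schedule, then asks which path a missing baseline affects.

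**Step 1. Mediator list against Table 2.**

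| Mediator named in the text | Table 2 row | Baseline | Week 1 | Week 5 | Post |
|---|---|---|---|---|---|
| Working alliance | "Working alliance (WAI-I") | – | – | X | X |
| Outcome expectations | "Outcome expectations (three items") | – | X | – | – |
| Perceived barriers | none | – | – | – | – |
| CBT skills | "CBT skills (CBT-SQ") | X | – | – | X |

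The other week 1 row, "Postmigration living difficulties (PMLD-short version"), is a different construct, which the article assigns to predictors and moderators. It does not stand in for barriers. Working alliance also lacks a baseline, but an alliance cannot exist before treatment; an expectation can.

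**Step 2. Order in time.** Baseline, then randomization ({16b}), then expectations at week 1, then the endpoint at post-treatment. A mediator of assignment has to be measured after assignment and before the outcome, and this order satisfies that.

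**Step 3. Which path is exposed.** Let T be arm, M0 prior expectation, M the week 1 score, Y0 and Y the baseline and post outcome. All coefficients are assumed for illustration, and M0, Y0 and the errors are independent standard normal:

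- M = 0.5·T + 0.6·M0 + 0.8·error
- Y = 0.3·T + 0.3·M + c·M0 + 0.5·Y0 + error

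The treatment-to-mediator path is a = 0.5. T is randomized and so independent of M0; omitting M0 leaves a unbiased.

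The true mediator-to-outcome path is b = 0.3. Regressing Y on T, M and Y0 without M0 gives

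b* = 0.3 + c × 0.6 / (0.6² + 0.8²) = 0.3 + 0.6c.

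- c = 0 (prior expectation has no effect of its own on outcome): b* = 0.30
- c = 0.3: b* = 0.3 + 0.18 = 0.48

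A simulation of 2,000 trials with N = 131, split on average 75:56, agrees. Without M0, a is 0.50 in both cases and b is 0.30 (c = 0) or 0.48 (c = 0.3). With M0 in the model, b is 0.30 in both. For c = 0.3 the product a × b would be 0.5 × 0.48 = 0.24 against a true 0.5 × 0.30 = 0.15. Higher HSCL-25 scores are worse, so b and c would both be negative in practice; reversing both signs leaves the relative bias unchanged.

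**Step 4. What other baseline measures could do.** Suppose baseline HSCL-25, self-efficacy and social support, used as covariates, explain a share R² of the variance of M0. The remaining bias is

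c × 0.6(1 − R²) / [0.36(1 − R²) + 0.64].

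At c = 0.3:

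- R² = 0: 0.18 / 1.00 = 0.18, so b* = 0.48
- R² = 0.5: 0.09 / 0.82 = 0.11, so b* = 0.41
- R² = 1: 0, so b* = 0.30

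The documents give neither c nor R².

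**The case against.** The strongest reply on outcome expectations is that week 1, after open allocation, is where a mediator belongs. That is correct. A reader might infer from the single post-allocation measurement that outcome expectations cannot support mediation at all. The documents do not support that: the time order is right, randomization identifies the treatment-to-mediator path, and an analysis is possible. Unmeasured mediator-outcome confounding is also a general limit of mediation analysis, which a baseline score reduces but does not abolish. Other baseline measures can absorb part of it, as Step 4 shows. What remains is that prior expectation, the most direct candidate confounder, could be measured cheaply and is not.

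On barriers, the shared citation makes it plausible that the three-item row covers both constructs. Table 2 also gives no separate row to some other small item sets, such as asylum-related variables or the question on ever having experienced a traumatic event. So a reader who infers that barriers will never be collected, or cannot be analysed, goes further than the article allows. The platform build is not described, and the cited source is not at hand. Against this, Table 2 names several constructs in one row elsewhere (distress, anxiety and depression share the HSCL-25 row), and here it names only expectations. The mismatch stands on either reading, because the article prints a detailed schedule that does not agree with its own mediator list.

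Finally, the analysis is exploratory, and Objectives {7} gives only working alliance and CBT skills as examples of mediators. That settles the severity but leaves the mismatch in place.

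**Conclusion.** The point holds in a limited form, and it is minor.

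- Perceived barriers are a named mediator without a row or time point in Table 2, unless the three-item outcome-expectations row covers them, which the article does not state.
- Outcome expectations are measured at a suitable time for a mediator but have no pre-allocation score. The treatment-to-mediator path is unaffected; the mediator-to-outcome path can be confounded by prior expectation.

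The size of the bias is unknown from the documents. The illustration (0.30 to 0.48 against a true 0.30) rests entirely on assumed coefficients. It disappears if prior expectation has no effect of its own on outcome, and it shrinks as other baseline covariates account for prior expectation. It shows the direction and mechanism and is not an estimate for this trial.

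**What to change.** 1. Add the three outcome-expectation items to the baseline questionnaire, keep week 1, and adjust the mediation regression for the baseline score. If this is not done, state as a limitation that the mediator-to-outcome path cannot be adjusted for prior expectation.
2. Reconcile the mediator list with Table 2 in one of three ways: give perceived barriers a row and a visit; state that the three-item row covers them and how the items divide; or delete them from the list.

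The cost is three more items at baseline, a few for barriers if they get their own row, and a table correction. The downside is a slightly longer baseline. Recruitment was due to start in November 2023; anyone already randomized would have no baseline expectation score, and this cannot be recovered later. For those participants the limitation would have to be stated in any case.
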